##### 3.5.1.1. Optimization objective

The optimal component settings will have to meet the following criteria: increase average baseline sleep duration on weeknights by ≥30 min for ≥75% of intervention weeks and for ≥50% of follow-up weeks. A 30-min increase in sleep duration has been shown to be feasible in our prior research (Mitchell et al., 2021) and has been shown to improve alertness and emotional regulation (Gruber et al., 2012) and to lower weight gain (Hart et al., 2022).

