### 3.6. Power calculation

#### 3.6.1. Aim 1

The primary outcome for Aim 1 is nighttime sleep duration (hours per night) on weeknights (measured daily by the sleep tracker). The “MOST” R package (FactorialPowerPlan) was used to determine the sample size needed to detect a 30 min per night difference in nighttime sleep duration on weeknights (alpha = 0.05; power = 0.8; pretest-posttest correlation of sleep duration = 0.7; and a standard deviation sleep duration = 0.7 h per night). The effect size and parameters were derived from our prior studies. The calculation accounted for detection of main effects plus all possible interactions. The power calculation revealed that a minimum sample size of 41 was needed for Aim 1.

#### 3.6.2. Aim 2

The primary outcome for Aim 2 is fat mass index (kg/m^2^) (measured at baseline, 6-months, and 12-months by DXA). The “MOST” R package (FactorialPowerPlan) was used to determine the sample size needed to detect a 0.25 kg/m^2^ reduction in fat mass index at 6-months and 12-months (alpha = 0.05; power = 0.8; pretest-posttest correlation of fat mass index = 0.9; and a standard deviation for fat mass index = 0.9). The effect size and parameters were derived from our prior studies. The calculation accounted for detection of main effects plus all possible interactions. The power calculation revealed that a minimum sample size of 282 was needed for Aim 2.

#### 3.6.3. Aim 3

The primary outcome for Aim 3 is nighttime sleep duration (hours per night) on weeknights (measured daily by the sleep tracker). It has been observed that male children sleep on average 12 min per night less than female children, and that African American/Black children sleep on average 33 min per night less than non-Latinx White children (Guglielmo et al., 2018; Billings et al., 2021; Min et al., 2021). We will determine if the effectiveness of the optimal component settings for sleep promotion differ by ≥20 min across sociodemographic factors. This calculation revealed that 286 participants are needed to detect a ≥20 min per night difference in the effectiveness of the optimal component settings for sleep duration by higher and lower sociodemographic levels. The calculation was completed in Stata (version 14.2) using the “power repeated” command to compute the sample size. The parameters used for the calculation were: alpha = 0.05, power = 0.8, number of repeated measures = 52, number of groups = 2, error variance = 1.1, and correlation = 0.7.

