### 3.7. Statistical plan

Under the intent to treat principle, we will use all available data and participants under the assumption of missingness at random. No participants will be excluded from the analysis except for the unlikely case of no outcome measurements for a participant. Final models will be adjusted for covariate dependent missingness due to dropout. We will examine sensitivity to the assumptions about the missing data mechanism.

#### 3.7.1. Aim 1

Mixed-effects linear regression models will be used to determine if the intervention components are associated with changes in weeknight sleep duration from baseline. The fixed model components will include indicators for each factor (with effect coding used to identify each component level), time in weeks, and all possible interactions between time and factors. The full model will be reduced to a more parsimonious model by selecting the main effects and interactions achieving a Type I error rate of alpha = 0.05.

#### 3.7.2. Aim 2

Mixed-effects linear regression models will be used to measures changes in fat mass index using the most parsimonious model from Aim 1 (i.e., optimal component settings for sleep promotion).

#### 3.7.3. Aim 3

The most parsimonious model from Aim 1 (i.e., optimal component settings for sleep promotion), will be expanded to determine if effectiveness differs by sociodemographic factors. The fixed model components will include indicators for each component (effect coding to represent the levels of each factor), time in weeks, the sociodemographic factor of interest, interactions between time, component(s), and sociodemographic factor. The sociodemographic factors that will be modeled include sex, race/ethnicity, and neighborhood context (poverty, sound, canopy cover, housing and population density, and street connectivity).

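### Section 3.7 calls the p<0.05 Aim 1 model the optimal settings and never applies the 30-minute criterion that Section 3.5.1.1 makes a requirement

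*Protocol article*

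**What the plan says.** Section 3.5.1.1 states a requirement: "The optimal component settings will have to meet the following criteria", and then the criterion, "increase average baseline sleep duration on weeknights by ≥30 min for ≥75% of intervention weeks and for ≥50% of follow-up weeks".

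Section 3.7.1 starts from a mixed model with effect-coded factors, time in weeks and "all possible interactions between time and factors". That model is then "reduced to a more parsimonious model by selecting the main effects and interactions achieving a Type I error rate of alpha = 0.05".

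Section 3.7.2 analyses fat mass index "using the most parsimonious model from Aim 1 (i.e., optimal component settings for sleep promotion"). Section 3.7.3 repeats the equation for Aim 3: "The most parsimonious model from Aim 1 (i.e., optimal component settings for sleep promotion), will be expanded" to include sociodemographic factors. Section 3.7 does not mention the 3.5.1.1 criterion.

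For the sample sizes of both Aim 1 and Aim 2, Section 3.6 says: "The calculation accounted for detection of main effects plus all possible interactions".

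**The concern.** The trial's product is the package that goes forward to a later randomized trial (Sections 4 and 5). The article gives two accounts of how that package is identified and does not join them. An analyst who follows 3.5.1.1 looks for settings with a large enough and lasting rise from baseline. An analyst who follows 3.7 keeps the significant terms and calls the result optimal. The two can reach different packages, or one of them can reach none.

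The rules also answer different questions. Every condition includes self-monitoring and active messaging (Table 1 and Section 3.3.4), so all conditions could rise together without any component mattering. Equally, a component could matter while no condition rises by 30 min. A list of significant terms is not in itself a setting.

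Aim 2 has a second consequence. Fat mass index is a primary outcome (Section 3.5.1). As 3.7.2 is written, its model holds only the terms that survived the screen on sleep, so a screened-out component gets no fat mass estimate, although the trial was sized to detect all factorial effects on that outcome.

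**Working it through.** **Inputs.** From Section 3.6.1: difference 0.5 h, SD 0.7 h, pretest-posttest correlation 0.7, alpha 0.05, power 0.80. From Section 3.6.4: 325 randomized, 10% attrition, so 325 × 0.9 = 292.5, taken as 292. Assumed because not stated: two-sided alpha, 16 equal cells, and one change score per child (the planned model is weekly).

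**Reproducing the plan's figure.** Variance of the change score = 2 × 0.7² × (1 − 0.7) = 0.294 h². For a 2⁴ factorial with 16 parameters, the noncentrality is N × (0.5/2)² / 0.294 on 1 and N − 16 degrees of freedom. Power is 0.799 at N = 40 and 0.810 at N = 41. The stated minimum of 41 reproduces exactly.

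**What the p<0.05 rule keeps at 292 children.**
- SE of a component effect = 2 × √(0.294/292) = 0.0635 h = 3.8 min.
- Smallest estimate kept = 1.96 × 3.81 = 7.5 min (6.9 min with baseline as a covariate, 9.6 min with no baseline adjustment).

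**False terms if nothing works.** Four factors give 4 main effects and 11 interactions, 15 terms. Treated as independent, the chance of keeping at least one is 1 − 0.95¹⁵ = 54%, with 15 × 0.05 = 0.75 expected. For the four main effects alone it is 1 − 0.95⁴ = 19%.

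**Can the rules disagree?** Illustrative true effects were simulated with N = 292, variance 0.294 and 4,000 runs. Only the 30-min level was checked, not the shares of weeks.
- *One component worth 12 min, average rise 10 min.* The best setting truly rises 10 + 12/2 = 16 min. In 92% of runs a term was kept while the best predicted setting stayed below 30 min.
- *Every condition rises 35 min and no component matters.* Every setting meets the 30-min level, yet 46% of runs kept no term, so the reduced model names no setting. The other 54% kept at least one false term.
- *Four components of 12 min each, average rise 10 min.* The best setting truly rises 10 + 4 × 6 = 34 min. A term was kept in nearly every run and the best prediction reached 30 min in 72%, so here the rules often agree.

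**Risk in the obvious remedy.** If settings are picked from saturated-model means, each has SE √(0.294/(292/16)) × 60 = 7.6 min, against √(5 × 0.294/292) × 60 = 4.3 min from a main-effects model. If all 16 conditions truly rise 20 min, the highest of the 16 means averages about 33 min. At least one passes 30 min with probability 1 − Φ(10/7.6)¹⁶, about 80%.

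**The case against.** The strongest reply is that the rules are two steps. Section 1.8 describes the optimization phase as finding settings that satisfy optimization criteria, and says the results are used to drop or adjust components. On that reading 3.7.1 screens terms and 3.5.1.1 then judges the settings; the detailed algorithm would belong in the full plan. This has force: the rules can be reconciled, and a reader who infers that they are irreconcilable goes too far. But the article does more than leave the link out. It twice states that the reduced model is the optimal settings, so a fuller plan that follows the sequence must override that text.

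Three further inferences are not supported.
- *That 7.5 min contradicts 30 min.* The first is a difference between levels of one component, the second a package's change from baseline. Four components of 7.5 min separate the best and worst conditions by 4 × 7.5 = 30 min.
- *That reported effects are inflated in general.* A true 5-min effect that passes the screen averages about 9.8 min, but it passes only 26% of the time. A true 10 min averages 11.6, 15 averages 15.2, and the planned 30 averages 30.0. Inflation is negligible from about 15 min upward.
- *That Aim 3 p-values are invalid.* Aim 3 tests interactions of components with sociodemographic factors. The Aim 1 screen does not use them, and with near-balanced effect coding they are almost uncorrelated with the terms it does use.

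It can also be said that Section 1.9 limits Aim 2 to the optimal settings by design, and that sizing for all effects is prudent when the survivors are unknown. That justifies testing the selected settings as the Aim 2 question. It does not require removing the other components from the model.

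**Conclusion.** The concern holds in this form: the article makes the 3.5.1.1 criterion a requirement, equates optimal settings with a p<0.05 model that need not meet it, and carries that model into Aims 2 and 3. A kept model need not contain any setting that reaches 30 min, and settings that all reach it may leave no term to keep. The 7.5-min threshold rests on the protocol's own inputs with a single change score per child; the weekly mixed model would alter it. The 54% holds only if there are no true effects and the 15 terms are independent. The simulated disagreement rates depend on illustrative effects. The textual conflict and the loss of fat mass estimates for screened-out components, as 3.7.2 is written, depend on none of these. This should be corrected before outcome data are analysed, because choosing a definition afterwards would weaken the main conclusion. It is a correctable fault of the analysis text, short of one that must block the trial.

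**What to change.** 1. Delete the equation of the reduced model with the optimal settings in Sections 3.7.2 and 3.7.3.
2. In 3.7.1, report component effects from the full effect-coded model.
3. Call a setting optimal only if its model-predicted weekly change meets the 3.5.1.1 criterion in both phases. Take predictions from a prespecified model, for example main effects plus interactions that are prespecified or clearly supported, and report them with confidence intervals. Do not simply take the highest of 16 saturated-model means, which is itself optimistic.
4. For Aim 2, fit all factorial effects to fat mass index with baseline fat mass index in the model, and test the selected settings as a prespecified contrast within it. Use the same contrast in Aim 3.
5. State that estimates for the selected settings come from the same children who were used to select them.

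These are changes of analysis text only, with no new data or participants. The cost is a few more estimated parameters against about 290 children, and wider intervals for predicted settings.

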## 3. Methods

### 3.1. Study design

A 2^4^-factorial design (i.e., 16 study conditions) will be used to address the study objectives (Table 1). A two-week run-in phase will be used to measure baseline sleep duration, a 6-month intervention phase will be used to measure changes in sleep duration from baseline, and a ≈5.5-month follow-up phase will be used to measure if there are lasting changes in sleep duration from baseline. Clinical measurements (e.g., DXA, 24 h dietary recalls) will be obtained at baseline, 6-months, and 12-months at the Children's Hospital of Philadelphia (CHOP).

**Table 1 T1:** The 2^4^ factorial study design.

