#### 3.3.3. Randomization and blinding

A computerized random number generated by the W2H platform will assign children to 1 of 16 study conditions. Block randomization will be used. Participants cannot be blinded to the interventions components to which they are exposed. The study coordinators will not be blinded because they will need to monitor intervention delivery and communicate appropriately with families. Investigators will be blinded, except the psychologist on the team who needs to direct the virtual study visit delivery for one of the intervention components.

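### The Aim 1 reduction rule has no hierarchy condition, so an interaction can stay after its parent component effect is dropped, which mainly distorts the size of the predicted effects that define the optimal settings

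*Protocol article*

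**What the plan says.** The trial is a "2^4^-factorial design (i.e., 16 study conditions) will be used to address the study objectives". For Aim 1, section 3.7.1 of the protocol article specifies a mixed-effects linear model of weeknight sleep duration. It has an indicator for each component ("with effect coding used to identify each component level"), and it also includes "time in weeks, and all possible interactions between time and factors". That model is then to be "reduced to a more parsimonious model by selecting the main effects and interactions achieving a Type I error rate of alpha = 0.05". The sentence sets one criterion, significance at 0.05, and applies it to main effects and interactions alike. It sets no condition on the parent terms of an interaction that survives.

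Section 3.7.2 analyses fat mass index "using the most parsimonious model from Aim 1 (i.e., optimal component settings for sleep promotion"), and section 3.7.3 expands the same model for Aim 3. The article therefore treats the reduced model and the optimal settings as one thing. Section 3.5.1.1 adds a separate requirement: a gain of at least 30 min in at least 75% of intervention weeks and at least 50% of follow-up weeks.

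**The concern.** Taken literally, the rule can leave an interaction A×C in the model with A removed. Under effect coding, the coefficient of A is half of A's effect averaged over the levels of C. Deleting it does not leave that average open; it fixes it at zero. The reduced model must then say that A helps at one level of C and does equal harm at the other, whatever the data showed. The same happens with time terms when component×component×time is kept without component×time.

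The purpose of Aim 1 is to choose settings from these predictions. A component that works in one context and does nothing in the other would have its benefit understated and a spurious loss overstated, and Aims 2 and 3 would carry the distorted model forward.

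**Working it through.** **Inputs.** From section 3.6.1: SD 0.7 h and "alpha = 0.05; power = 0.8; pretest-posttest correlation of sleep duration = 0.7". From section 3.6.4: 325 randomised with 10% attrition, so 325 × 0.9 = 292.5, taken as 292. Section 3.3.3 says only "Block randomization will be used"; equal allocation to the 16 conditions is assumed. A two-sided test and -1/+1 coding are also assumed. The calculation uses one change score per child and no time term.

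**The plan's own figure.** Section 3.6.1 sizes Aim 1 to "detect a 30 min per night difference in nighttime sleep duration on weeknights".
- Change-score SD = 0.7 × √(2 × (1 - 0.7)) = 0.542 h = 32.5 min.
- A 0.5 h difference is a coefficient of 0.25 h. With 16 coefficients, the F test has 1 and N - 16 df and noncentrality N × 0.25² / 0.542².
- Power is 0.799 at N = 40 and 0.810 at N = 41. The stated minimum of 41 is reproduced, so these inputs are the right ones to use.

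**Selection cut-off at N = 292.**
- SE of a coefficient = 32.5 / √292 = 1.90 min, the same for every term when the design is balanced.
- A term is dropped if its estimate is below 1.96 × 1.90 = 3.73 min. A simple effect contains twice the coefficient, so one dropped term moves it by at most 2 × 3.73 ≈ 7.5 min.

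**Worked example (effect sizes assumed for illustration).** Component A adds 20 min when C is active and 0 otherwise. The simple effects are 2(A + AC) = 20 and 2(A - AC) = 0, so both coefficients are 5 min.
- Chance that each is significant: about 0.75. Chance that AC is kept and A dropped: 0.75 × 0.25 ≈ 0.19.
- In those trials the mean estimates are AC ≈ 5.8 and A ≈ 2.6.
- Reduced model: ±2 × 5.8 = +11.6 and -11.6 min.
- Same data with A restored: 2 × (2.6 + 5.8) = +16.8 and 2 × (2.6 - 5.8) = -6.4 min.
- Truth: +20 and 0. The hierarchical prediction is closer in both cells.

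With a different assumption, +20 and +5 min, the pattern occurs in 4.7% of trials, and the reduced model predicts about -10.5 min where the truth is +5.

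**Sign.** With one interaction kept and A dropped, the estimate of A is smaller in absolute size than that of AC. A + AC and A - AC therefore have the signs of AC and -AC whether or not A is in the model. Simulation of five assumed effect patterns (40,000 runs each) gave 0 reversals in about 789,000 such contrasts. Where two or more interactions of one factor were kept, restoring its main effect reversed roughly 9–16% of that factor's simple effects in most cases.

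**Choice of settings.** If all four components have 10-min main effects, the mean loss from picking a cell that is not the best is 5.5 min under the rule as written. It is about 5.2 min if only parents of retained interactions are restored, and 1.8 min if all four main effects are also kept. Across the patterns tried, restoring parents alone gained from nothing to 3.7 min.

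**The case against.** The strongest reply is that the article is a condensed document. A hierarchy rule may stand in the full protocol or analysis plan, and the sentence is compatible with hierarchical reduction. That is fair as to intent: the article does not say that parent terms are to be removed, only that terms are selected on significance. But it does state a criterion, and it identifies the outcome with the optimal settings. Followed as written, that criterion permits the defect, so the sentence itself needs the correction.

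Three stronger readings are tempting, and the documents do not support them.
- A reader might infer that the rule generally gets signs wrong. Effect coding makes the terms near-orthogonal with equal standard errors. In the example the hierarchical model also predicts a loss (-6.4 min) where the truth is 0. That wrong sign comes from sampling error in A among the selected trials, not from the missing hierarchy.
- A reader might count how often the final model breaks hierarchy when nothing works. That is 1 - 0.95^11 ≈ 43%, simply the chance of at least one false positive among 11 interactions. It measures multiplicity, not this defect.
- A reader might argue that a component's main effect becomes its effect at week 0 and is therefore selected arbitrarily. The article does not give the origin of week. If week 0 is baseline, that term is a baseline difference, expected to be zero under randomisation, and dropping it does no harm. What matters then is losing component×time while keeping component×component×time.

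It also stands that 7.5 min is a quarter of the 30-min target, that section 3.5.1.1 imposes a further test on the settings, and that much of the gain in choosing settings comes from keeping all four component effects rather than from restoring parents alone.

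**Conclusion.** The concern holds in a limited form. The stated reduction rule can keep an interaction without its parent, and it then forces equal and opposite predicted effects. The distortion is chiefly of size: up to about 7.5 min per dropped term, and +12/-12 instead of about +17/-6 min in the example, a pattern expected in about 19% of trials under that assumption. Reversal of sign caused by the rule is confined to factors with several retained interactions, or to marked non-orthogonality.

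These figures rest on the plan's SD and correlation, 292 analysed, equal allocation, change scores and illustrative effects. They were not computed for the weekly longitudinal model, where orthogonality also depends on how week is coded and on missing data. The point is worth correcting because Aims 2 and 3 inherit the model and the correction is cheap; it does not threaten the design.

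**What to change.** In section 3.7.1, add to the reduction rule that the final model keeps all four component effects (as component-by-time terms if week 0 is baseline) and every lower-order term of any retained interaction, including the time terms. State that the settings are read from the predicted means of that hierarchical model, and let sections 3.7.2 and 3.7.3 refer to it.

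The cost is a sentence or two of wording and a slightly larger final model. Precision should hardly suffer, because effect-coded terms are near-orthogonal when the conditions are of similar size. Sample size and data collection do not change.

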## 4. Anticipated results

Expected outcomes include identifying optimal component settings for sleep promotion in children. This increase will be clinically meaningful with improvements in fat mass trajectories detected. Importantly, the platform will have broad impact by promoting sleep health equity across sociodemographic groups (Jackson et al., 2020). With the optimal settings identified, we will be able to determine the effectiveness of the final intervention package under the evaluation phase of the MOST framework in a future trial.

## 5. Discussion

Our long-term goal is to develop, evaluate and continually improve pediatric sleep extension interventions that are scalable and can be widely disseminated in pediatric primary care. Upon completion of this study, we anticipate that we will have optimized the first behavioral sleep extension package for pediatric primary care to help prevent childhood obesity. A potential immediate next step will be to complete the evaluation phase of the MOST framework, where we will conduct an RCT to determine if our optimized intervention package causes improvements in sleep duration and lower gains in fat mass over time, equitably across sociodemographic groups. We will also remain committed to the MOST framework and the related continuous optimization principle. All behavioral interventions can be improved, and we will seek to complete another cycle of optimization for equitable sleep promotion in other obesity related disease areas.

